### Sample size

The sample size was calculated using the STATA 11 program, using a study conducted by Choudhary et al. [31] as the basis. Scores on the Quality of Upper Extremity Skills Test (QUEST) were used for the calculation. Based on the mean and standard deviation values of the experimental group prior to intervention (mean: 76.4; standard deviation: 9.2) and after the intervention (mean: 87.2; standard deviation: 9.4), a bidirectional alpha of 0.05 and 80 % test power, a minimum of 13 children were deemed necessary for each group. The sample will be increased by 20 % to compensate for possible dropouts, leading to 17 children in each group (overall sample: 34 participants).

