### Statistical analysis

Statistical analysis will be performed using intention-to-treat analysis. If data losses occur during the study, ‘last observation carried forward’ analysis will be employed to adjust the missing data in the follow-up evaluations. The data will be expressed as mean and standard deviation values. The two intervention groups will be analyzed for differences in anthropometric characteristics as well as clinical and functional variables using the chi-square test for categorical variables and the *t* test for continuous variables. Analysis of covariance (ANCOVA) will be employed to evaluate the effects of transcranial direct current stimulation on the outcome variables of upper limb function. For all analyses, the fixed independent variables will be group (active and sham transcranial direct current stimulation) and evaluation (before the intervention, after the intervention, at 1 month follow-up, and at 3 month follow-up). The dependent variables at baseline will be considered covariables: QUEST, outcomes obtained from three-dimensional movement analysis, electromyography, and spasticity. The ANCOVA will be used to compare effects after the interventions (active versus sham transcranial direct current stimulation), adjusting individual performance prior to transcranial direct current stimulation. This model was considered to be an advantageous approach for statistical analysis considering the nature of the study (randomized with a relatively small sample). Cohen’s *d* (effect size) will be calculated based on the difference in values between baseline and the post-intervention evaluation, with the comparison of the groups. Statistical significance will be considered for *P* < 0.05. Data will be organized and tabulated using the Statistical Package for the Social Sciences (SPSS, v.19.0).

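### The ANCOVA lists the pre-intervention evaluation as an outcome level and also uses it as the covariate, against its stated aim of comparing effects after the interventions

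*Protocol article*

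**What the plan says.** All of this is in the protocol article, Statistical analysis section, which fixes one model for all analyses.

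- Between-group factor: "the fixed independent variables will be group (active and sham transcranial direct current stimulation").
- Second fixed factor, which has four levels, the first being the baseline assessment: "evaluation (before the intervention, after the intervention, at 1 month follow-up, and at 3 month follow-up").
- Covariate: "The dependent variables at baseline will be considered covariables", followed by QUEST, the movement-analysis outcomes, electromyography and spasticity.
- Purpose: "The ANCOVA will be used to compare effects after the interventions" (active versus sham), "adjusting individual performance prior to transcranial direct current stimulation".
- Effect size: Cohen's *d* "will be calculated based on the difference in values between baseline and the post-intervention evaluation", compared between groups.

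The section names no group-by-evaluation term and no within-child error term. It does not say which term or contrast tests Hypothesis 1.

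**The concern.** A baseline-adjusted analysis of repeated outcomes has the post-baseline values on the left-hand side and the baseline value on the right. Here the baseline value is on both sides. For the baseline rows, outcome and covariate are the same number, so those rows carry no information about treatment and leave little residual. The stated purpose fits a factor with post-baseline levels only, so the paragraph contradicts itself.

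Two results could be affected, and they are different quantities. A group effect averaged over the four levels includes one level at which the true difference is zero by randomisation. A contrast at a single visit avoids that averaging, but it can borrow a residual variance that the baseline rows have made too small. The model governs every outcome, so the published adjusted differences and their intervals depend on how the contradiction is resolved.

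**Working it through.** **The plan's own figure.** The Sample size section gives QUEST "prior to intervention (mean: 76.4; standard deviation: 9.2") and "after the intervention (mean: 87.2; standard deviation: 9.4"). The difference is 87.2 − 76.4 = 10.8 and the common SD is √((9.2² + 9.4²)/2) = 9.30. For a two-sided 5% two-sample *t* test, the noncentral *t* gives power 0.776 with 12 per group and 0.811 with 13. So 13 per group reproduces, and 13/0.80 = 16.25 rounds up to 17. Neither figure uses the ANCOVA model.

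**Inputs for the check.** 17 per group and SD 9.3. Equal correlation ρ between any two evaluations is an assumption, since the article gives none; the range is 0.3 to 0.9, except where stated.

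**1. Group main effect, size.** With true differences d₁, d₂, d₃ at the three post-baseline evaluations, the four-level average is (0 + d₁ + d₂ + d₃)/4, which is ¾ of their mean.
- Constant 10.8: 0.75 × 10.8 = 8.1 (simulated 8.09–8.14, against 10.78–10.85 with three levels).
- Fading 10.8, 5.4, 2.7: 18.9/4 = 4.7 with four levels, 18.9/3 = 6.3 with three (simulated 4.74 and 6.32).

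**2. Group main effect, test with a between-child error term.** Let B be a child's baseline and M the mean of the three later values. The four-level child mean is (B + 3M)/4. Regressed on group and B, the B/4 part is absorbed by the covariate. The group estimate and its SE are therefore both exactly 0.75 times those from M, and *t*, *p* and power are identical. Simulation agrees: at ρ = 0.7 the SE is 1.34 against 1.79; for a true difference of 5, power is 0.771 with either model; type I error is 0.043–0.052.

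**3. Group main effect, interval.** The interval is centred 0.25 × d too low. Given B, M has variance σ²[(1 + 2ρ)/3 − ρ²]. At ρ = 0.7 this is 86.49 × 0.31 = 26.8, so the four-level SE is about 0.75 × √(2 × 26.8/17) = 1.33. For d = 10.8 the shift is 2.7, about two SEs, so about half the intervals miss.

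| True difference | ρ | Coverage, four levels | Coverage, three levels |
|---|---|---|---|
| 6 | 0.5 | about 85% | about 95% |
| 6 | 0.7 | about 81% | about 95% |
| 10.8 | 0.5 | about 61% | about 95% |
| 10.8 | 0.7 | about 50% | about 96% |

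**4. Visit contrast, one residual pooled over all rows.** This adds a group-by-evaluation term, which the article does not name. The contrast itself is not shrunk (10.7–10.9 for a true 10.8). The common slope is b = (1 + 3ρ)/4 instead of ρ. In units of σ², the residual variance is (1 − b)² in baseline rows and 1 − 2bρ + b² in later rows. At ρ = 0.7:
- b = 0.775; baseline rows 0.051; later rows 0.516
- pooled residual (0.051 + 3 × 0.516)/4 = 0.400
- SE ratio about √(0.400/0.516) = 0.88

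Simulation, 4,000 null trials per correlation:

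| ρ | Model SE / true SE, four levels | Type I error, four levels | Type I error, three levels |
|---|---|---|---|
| 0.3 | 0.89 | 0.087 | 0.059 |
| 0.5 | 0.90 | 0.070 | 0.045 |
| 0.7 | 0.87 | 0.089 | 0.054 |
| 0.9 | 0.86 | 0.093 | 0.052 |

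**5. Group main effect, one pooled residual.** Type I error is 0.086–0.166 with four levels and 0.107–0.168 with three. The cause is the ignored correlation within children, so removing the baseline level does not cure it.

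**6. Repeated-measures group-by-evaluation F test with the baseline covariate.** Type I error is 0.049–0.059, so it is not materially inflated.

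**The case against.** The strongest reply is that the harm is conditional and mostly mild. The article never says that the group main effect tests Hypothesis 1. The stated aim already points to post-treatment comparisons, and Cohen's *d* is based on the change from baseline to the post-intervention evaluation, outside the four-level averaging. A condensed article may leave the error structure to a fuller plan. With a between-child error term the main-effect test is unchanged, and any shrinkage is toward zero. If each visit is regressed separately on group and baseline, a baseline column changes nothing at the other visits.

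All of that stands, and it rules out several stronger readings that a reader might infer:

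- *That one reported effect is both shrunk by a quarter and given too small an error because of the baseline rows.* The shrinkage belongs to the averaged main effect. The SE deflation caused by the baseline rows belongs to a visit contrast with a pooled residual, which is not shrunk.
- *That the trial loses power or its test becomes invalid in every case.* Steps 2 and 6 show otherwise.
- *That deleting the baseline level is enough.* Step 5 shows it is not if correlation within children is ignored. Nor does a three-level average equal the effect at the post-treatment visit when the effect fades (6.3 against 10.8), so the contrast still has to be named.

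The reply does not remove the contradiction. The four levels and the covariate are both stated rules, not omitted detail. Group is the only between-group term that the text names. A valid *p* value does not repair an adjusted difference that is a quarter too small, or an interval that misses the true mean difference too often.

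**Conclusion.** The point holds in a limited form. The Statistical analysis section uses baseline as an outcome level and as the covariate, against its own stated aim.

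- If the group main effect is reported, it estimates three quarters of the mean post-baseline difference. The nominal 95% interval covers that mean difference in about 81–86% of trials for a 6-point effect and 50–61% for 10.8 points (ρ of 0.5 and 0.7, between-child error term). The *p* value and power are unaffected.
- If a visit contrast is reported with one residual pooled over all rows, the estimate is right, but its SE is about 10–14% too small and type I error is about 7–9% instead of about 5% (ρ from 0.3 to 0.9).

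The factor of three quarters is exact algebra. The coverage and error rates rest on 17 complete children per group, SD 9.3 and equal correlations, which are assumed. The document does not settle which of the two cases applies. The 13 per group, or 17 with the dropout allowance, is unaffected.

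**What to change.** In the Statistical analysis section:

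1. Delete the pre-intervention assessment from the levels of evaluation, leaving post-treatment, 1 month and 3 months.
2. Keep each outcome's own baseline value as the covariate.
3. State that the repeated measures are modelled with a within-child error structure. This is needed in addition to step 1.
4. Name the baseline-adjusted active-minus-sham contrast that tests Hypothesis 1, with its evaluation time or times.

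The cost is one or two sentences. No new data, assessments or children are needed. The article reports that recruitment was under way at submission, so the change should be made and dated before anyone sees unblinded results.

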## Discussion

This paper presents a detailed description of a prospective, randomized, controlled, double-blind, clinical trial designed to demonstrate the effects of combining transcranial direct current stimulation over the primary motor cortex and functional training of the paretic limb in children with cerebral palsy classified at levels I, II, or III of the Manual Ability Classification System. The results will be published and evidence found may contribute to the use of transcranial stimulation for this population.

This study protocol used defining standard protocol items for clinical trials. SPIRIT 2013 Statement [44].

## Trial status

Patients are being recruited at the time of submission.

## Abbreviations

ANCOVA, analysis of covariance; CONSORT, Consolidated Standards of Reporting Trials; QUEST, Quality of Upper Extremity Skills Test; ReBEC, Brazilian Registry of Clinical Trials; SPSS, Statistical Package for the Social Sciences
